### Data collection and management

After the procedure, the enrolled patients will be visited for evaluation and management of underlying diseases, routine assessments, and optimal medical therapy. Clinical follow-ups will be performed at 1, 3, 6, and 12 months and telephone contacts will be performed every month till the end of the study. An assessment of angina status, cardiovascular drug use, and any serious adverse events will be recorded during these clinical follow-up visits. Participant files are to be stored in numerical order and stored in a secure and accessible place and manner. Files will be scanned and data will be recorded in computer-based data system used for patient data gathering and archiving. This program is well encrypted.

### Statistical analysis

Continuous variables will be presented as mean ± SD and categorical variables will be presented as counts and percentages. The comparison of categorical variables will be conducted using either the χ² test or Fisher’s exact test. To compare continuous variables, the Student’s t-test or the Wilcoxon rank-sum test will be used for non-normally distributed data. The statistical analyses will be carried out using Stata version 18.0 (StataCorp LLC, College Station, Texas, USA). All primary and secondary endpoints will be analyzed both on an intention-to-treat basis, determined by allocation. Cumulative event rates will be estimated with the Kaplan-Meier method. The Cox log-rank approach will be utilized to compare the incidence of endpoints, specifically focusing on the time-to-first-event analyses. Patients lost to follow-up will be censored at the time of the last known contact. The null hypothesis will be evaluated on the intention-to-treat population using inferiority statistics. If the upper limit of the one-sided 95% confidence interval of the difference is less than the prespecified non-inferiority margin of 1%, ticagrelor monotherapy will be considered non-inferior to the conventional 6-month DAPT regimen. A subgroup analysis will be conducted for clinically relevant factors such as age, sex, comorbidities, prior use of aspirin or P2Y12 inhibitors, lesion or procedural characteristics, and other risk indicators. A two-sided test will be used for all hypotheses testing at a 5% significance level. The results of this study will be reported in accordance with CONSORT statement. Statistical analysis and reporting of trial results will follow the estimand framework [24].

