### Modifications

Follow-up visits are scheduled at 1, 3, 6, and 12 months after the PCI procedure. If adverse events occur that require modifications to antiplatelet therapy or hypersensitivity reactions confirmed by the Data Safety and Monitoring Board (DSMB) and Trial Management Committee (TMC), drug consumption will be discontinued. These events will be recorded as study outcomes or adverse events. If the DSMB and TMC adjudicate these events as potentially leading to non-adherence to medication, the intervention group will be switched to standard care. The drugs responsible for these events will be replaced with safe and effective alternatives in both groups. Data from participants who experience such events will be censored at the time of the event to ensure accurate statistical analysis. Dyspnea, the most common side effect of ticagrelor, will be carefully monitored and recorded during follow-up visits. In case of severe dyspnea which may lead to non-adherence to the medication, the patient will be switched from the experimental therapy to the standard regimen. Non-severe dyspnea will be managed using conservative strategies like recommending caffein, theophylline, or inhaled bronchodilator in more severe cases.

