### Sample size

This study is designed to compare 6- and 12-month ticagrelor monotherapy to the conventional DAPT treatment in terms of efficacy and safety. We hypothesize that ticagrelor monotherapy is non-inferior for safety and efficacy to the DAPT regimen. The null hypothesis is the superiority of the standard DAPT regimen for both safety and efficacy primary endpoint. Based on the results of the international trials (GLOBAL LEADERS, STOP-DAPT-2, and TICO trials) and related article in our country (19) we anticipate that 2% of patients in the control and treatment arm will reach the co-primary efficacy endpoint. The non-inferiority margin is assumed to be 50% of the mentioned cumulative incidence (1%). The level of significance (one-sided alpha) and power (1-β) of the study were considered 5% and 80% respectively. Based on these assumptions, 2424 patients are required for each arm of the ideal study. Taking into consideration of loss to follow-up cases (10%), we have to enroll 5400 patients with 1:1 randomization to each arm in the ideal study. The formula that has been used for these calculations is shown in Formula 1 (20). However, due to the limited number of cases referred to our center and the safety uncertainties of the project, we will first conduct the initial phase of the study. We estimated that a total of 400 patients would be referred to our center for CCS management over a three-month period (the expected recruitment time for initial phase). With the goal of reaching the target sample size within approximately three years, the suitable sample size for the initiation phase is calculated to be about 180 patients in each arm of the study using Formula 2.

**Fomula 1**: $\backslash (N=2\;\times \;{\left(\frac{Z_{1-\alpha }+Z_{1-\beta }}{\delta_{0}}\right)}^{2}\times p\;\times (1-p).\;\backslash )$ N = size per group; p = the response rate of standard treatment group; z(x)= the standard normal deviate for a one or two sided x; δ0 = a clinically acceptable margin

**Fomula 2**: $\backslash (n=\;\frac{n_{0}}{1+\;\frac{\left(n_{0}-1\right)}{N}}\;\backslash )$. n=suitable sample size for the study; n0=ideal sample size x; N= total patients available

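### The non-inferiority decision rests on the intention-to-treat set alone: a second analysis set is announced but never named, and non-adherence without a formal switch can favour the claim

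*Protocol article*

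**What the plan says.** The Statistical analysis section of the protocol article says: "All primary and secondary endpoints will be analyzed both on an intention-to-treat basis, determined by allocation". It continues: "The null hypothesis will be evaluated on the intention-to-treat population using inferiority statistics". Non-inferiority is declared if the upper one-sided 95% confidence limit of the difference lies below 1 percentage point. The section also commits to the estimand framework. No per-protocol, as-treated or on-treatment set appears anywhere in the article.

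Four other places bear on the point:

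- **Discussion:** names reduced compliance because of dyspnoea as a main disadvantage of ticagrelor.
- **Outcomes:** lists drug adherence only as an ancillary endpoint.
- **Modifications:** if dyspnoea is severe, "the patient will be switched from the experimental therapy to the standard regimen". Participants with adverse events that force a change of antiplatelet therapy are censored at the event.
- **Treatment of missing values:** a patient whose medication is switched is deemed to have reached the study endpoint at the switch, and the time after it is not analysed.

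**The concern.** In a superiority trial, non-adherence usually works against the claim, so intention-to-treat is the cautious choice. In a non-inferiority trial that protection is lost, because anything that makes the arms more alike can help the claim. A second analysis restricted to patients who took their assigned drug is the usual check, and the broken sentence reads as if one was meant.

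The exposed group is patients who miss or stop tablets without an adjudicated switch. No rule in the article censors or removes them. They stay in the analysis by allocation with all their follow-up. Two examples show how this can favour non-inferiority:

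- **Bleeding:** if ticagrelor caused more major bleeding, patients not taking it would lower the rate in their arm.
- **Efficacy:** missed tablets in the control arm could raise the control event rate and so narrow the difference.

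At stake is a non-inferiority claim that rests on a single analysis, with nothing in the published rule to show whether poor adherence produced it.

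**Working it through.** **1. Inputs (Sample size section).** "The level of significance (one-sided alpha) and power (1-β) of the study were considered 5% and 80% respectively". The event rate: "we anticipate that 2% of patients in the control and treatment arm will reach the co-primary efficacy endpoint". The margin is half of that rate, 1 percentage point absolute. The article gives no non-adherence share, so the share f below is an assumption.

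**2. The plan's own figure.** Formula 1: N = 2 × ((z₀.₉₅ + z₀.₈₀)/δ)² × p(1 − p) = 2 × ((1.645 + 0.842)/0.01)² × 0.02 × 0.98 = 2,423.6, rounded up to 2,424. This agrees with "2424 patients are required for each arm of the ideal study". Allowing for 10% loss, 2,424/0.9 gives 2,694 per arm, or 5,388 in total, close to the stated 5,400. The sample size is not in dispute.

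**3. Illustration of dilution.** Let the control rate be p₀ = 0.02 and the true on-treatment ticagrelor rate 0.03, exactly at the margin. A share f of the ticagrelor arm has the control risk from day 0, with all follow-up kept. Then

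- p₁ = 0.02 + 0.01 × (1 − f)
- SE = √[p₀(1 − p₀)/n + p₁(1 − p₁)/n]
- P(non-inferiority declared) = Φ[(0.01 − (p₁ − p₀))/SE − 1.645]

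For f = 10% and n = 2,424: p₁ = 0.029, SE = √[(0.0196 + 0.02816)/2,424] = 0.00444, and Φ(0.001/0.00444 − 1.645) = Φ(−1.42) = 7.8%.

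| f | 2,424 per arm | 180 per arm |
|---|---|---|
| 0 | 5.0% | 5.0% |
| 10% | 7.8% | 5.7% |
| 15% | 9.6% | 6.0% |
| 20% | 11.7% | 6.4% |

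As a check, with equal rates of 2% the same formula returns 80% power at 2,424 per arm.

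**4. Do formal switches fit this model?** Set the sections side by side:

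- *Statistical analysis:* analyse by allocation.
- *Modifications:* censor at the event.
- *Treatment of missing values:* the study endpoint is reached at the switch, and later time is dropped.

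Under either of the last two, time on the control regimen after a switch is not analysed in the ticagrelor arm, so it cannot dilute the comparison.

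If reaching the endpoint means an endpoint event, the bias runs the other way. With truly equal drugs at 2% and switches in the ticagrelor arm only, a switched share s gives that arm a rate of s + 0.02(1 − s), a difference of 0.98s. The margin is used up at s = 0.01/0.98 = 1.02%. At 2,424 per arm, the chance of showing non-inferiority falls from 80% to 33% at s = 0.5% and to 5.5% at s = 1%.

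If the phrase means only the end of follow-up, the issue is informative censoring, whose size and direction the documents do not allow one to compute.

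**The case against.** The strongest reply has four parts.

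- **Switches.** A reader might infer that moving ticagrelor patients to the standard regimen makes the arms alike and so produces false non-inferiority. The documents do not support this. Follow-up after a switch is dropped, and on one reading the switch counts against ticagrelor. This objection stands in full.
- **Stopping is not crossing over.** A patient who simply stops ticagrelor is not on dual therapy, and nothing in the article gives that patient the control risk. The Background section credits dual therapy with fewer ischaemic events, so stopping in one arm could widen the efficacy difference. This stands as far as the direction for efficacy is concerned. It does not remove the bleeding route or the effect of missed tablets in the control arm.
- **Size.** The 7.8% to 11.7% range needs the full sample, day-0 dilution and shares the article does not give. The Recruitment section expects good compliance. In the initial phase of about 180 per arm the rise is small. This stands, and the figures are illustrative only.
- **Convention and unseen documents.** 'Both' may be a stray word, a per-protocol set may be defined in an analysis plan not shown, and requiring success in both sets is one convention among several. The first two are possible. Even so, the article does state the decision set and the decision rule, and the sentence that should name the sets is incomplete as printed. The third is accepted, and the fix allows for it.

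**Conclusion.** The point holds in a limited form. The sentence is incomplete, the decision rule names one set, and non-adherence without a formal switch stays in that set and can bias either primary comparison towards non-inferiority. For efficacy, neither the direction nor the size can be settled from the documents. The table is a sensitivity illustration. It assumes a true difference at the margin, 10% to 20% of the ticagrelor arm at the control risk, and dilution from day 0; later non-adherence would dilute less. It should not be read as the trial's actual error rate, nor as an effect of formal switches.

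A separate defect is that the analysis labelled intention-to-treat is not one for switched patients. Two sections discard their later follow-up and do not clearly agree on what the switch itself counts as, which sits badly with the promised estimand framework. The change is worth making because it is specific and cheap, and because it matters to the interpretation of a non-inferiority result.

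**What to change.** 1. Complete the sentence so that it names two bases, intention-to-treat and per-protocol. Define the per-protocol set by assigned drug actually taken and no prohibited antithrombotic.
2. Report the 1-point non-inferiority comparison in both sets. Let a claim rest on consistent results, and explain any disagreement. Whether success in both sets is a strict condition is for the trial team to decide and state in advance.
3. Reconcile Modifications, Statistical analysis and Treatment of missing values on how switched patients are analysed, so that the intention-to-treat analysis keeps their follow-up by allocation. State what reaching the study endpoint at a switch means. Once that follow-up is kept, switches can dilute the intention-to-treat comparison, which makes the second set more useful.

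The cost is one more analysis and a few sentences. Formula 1 and the 2,424 per arm need not change, but power is somewhat lower if both sets must agree. The per-protocol comparison is not fully randomised, so it serves as a check on the intention-to-treat result and does not replace it.

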### Treatment of missing values

The primary analysis of the study endpoints will not be covariate-adjusted. No imputation methods will be used to infer missing values of baseline variables. For the study endpoints, we will censor patients lost to follow-up and regard them as not having the primary endpoint when estimating Kaplan–Meier event rates. If a medication switch occurs, the patient will be considered to have reached the study endpoint at the time of the switch, and the remaining time in the study will not be included in further analysis.

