### Concomitant care

The administration of any antiplatelet or anticoagulant other than study pills is prohibited. The prescription of additional medications for the prevention or treatment of other conditions, according to current guidelines, is permitted only if there is no interaction with the study medications. If a patient requires anticoagulant therapy that interferes with the study drugs due to a specific illness or event, the event will be recorded, and the patient will be censored. At each follow-up visit, patients will be asked about any new medications, illnesses, signs, or symptoms they experience during the study. Medication adjustments will be made as necessary to prevent any impact on the trial results.

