### Outcomes

The co-primary efficacy endpoint is a composite of cardiac death, MI, stroke, stent thrombosis, and the need for revascularization. The secondary endpoints are all-cause death, occurrence of MACE including cardiac death, stroke (ischemic, hemorrhagic, or unknown), MI, arrhythmia, and other component of the co-primary endpoint. The primary safety endpoint is any Bleeding Academic Research Consortium (BARC) bleeding type 3 or 5 after PCI. The secondary safety endpoint is the occurrence of BARC type 1–5 bleeding. Ancillary endpoints are other adverse events including dyspnea, drug adherence, and reaction. All endpoints will be evaluated in each follow-up visit and the results of the analysis of endpoints will be reported at the end of 6- and 12- months post PCI. All events will be adjudicated by DSMB and TMC.

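### The rules for patients who switch medication or are censored at an adverse event conflict with the intention-to-treat test of non-inferiority, on either reading of the switch rule

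*Protocol article*

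**What the plan says.** Four parts of the protocol article bear on a patient who stops or changes the allocated drug.

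- **Treatment of missing values:** "If a medication switch occurs, the patient will be considered to have reached the study endpoint at the time of the switch". Follow-up after that point is then dropped, in these words: "the remaining time in the study will not be included in further analysis".
- **Modifications:** for adverse events that require a change of antiplatelet therapy, and for confirmed hypersensitivity, "Data from participants who experience such events will be censored at the time of the event to ensure accurate statistical analysis".
- **Concomitant care:** for a patient who comes to need an interfering anticoagulant, "the event will be recorded, and the patient will be censored".
- **Statistical analysis:** "All primary and secondary endpoints will be analyzed both on an intention-to-treat basis, determined by allocation", and "The null hypothesis will be evaluated on the intention-to-treat population using inferiority statistics". The only reason for censoring named there is loss to follow-up, at the last known contact. The section also commits to the estimand framework.

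Outcomes defines the endpoint: "The co-primary efficacy endpoint is a composite of cardiac death, MI, stroke, stent thrombosis, and the need for revascularization". A medication switch is not a component.

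**The concern.** A switch is an intercurrent event, and the analysis must treat it in one way. Here the text supports three results for the same patient: an event at the switch, censoring at the switch or its cause, or continued follow-up by allocation. The last is what intention-to-treat implies, although Statistical analysis never mentions switches.

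Switching is also unlikely to be balanced. Modifications calls dyspnea the most common side effect of ticagrelor and foresees a move to the standard regimen when it is severe. The same section allows responsible drugs to be replaced in both groups, so control patients can switch too, but the only named side effect that triggers a switch belongs to the ticagrelor arm.

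The two departures from intention-to-treat can act in opposite directions. Counting switches as events works against ticagrelor if it has more of them. Censoring can favour it if ischemic events follow the switch. A choice between the rules made after data are seen would undermine a non-inferiority claim.

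**Working it through.** **Inputs from the protocol (Sample size, Statistical analysis).** Composite risk 2% in both arms, margin 1 percentage point (pp), one-sided alpha 5%, power 80%. Non-inferiority is declared if the upper one-sided 95% limit of the difference is below 1%.

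**Assumed, because the documents give no figure.** The proportions switching and the risk after a switch.

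**1. The plan's own figure.** Formula 1: N = 2 × ((1.645 + 0.842)/0.01)² × 0.02 × 0.98 = 2424 per arm, as stated. The standard error (SE) of the difference is √(2 × 0.02 × 0.98/2424) = 0.402 pp. With a true difference of 0, the expected upper limit is 1.645 × 0.402 = 0.66%, and the chance of success is Φ(1/0.402 − 1.645) = 80%. This calculation contains no switch component.

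**2. Switch counted as an event.** With switch proportion s, independent of the composite, the arm's risk is 1 − (1 − 0.02)(1 − s). The chance of success is Φ((1 − difference)/SE − 1.645), in pp, with unpooled SE and 2424 per arm.

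| Switching, ticagrelor vs control (assumed) | Risk | Difference | Expected upper limit | Chance of non-inferiority |
|---|---|---|---|---|
| none | 2.00% vs 2.00% | 0 | 0.66% | 80% |
| 1% vs 1% | 2.98% vs 2.98% | 0 | 0.80% | 66% |
| 2% vs 1% | 3.96% vs 2.98% | 0.98 pp | 1.84% | about 5% |
| 5% vs 1% | 6.90% vs 2.98% | 3.92 pp | 4.94% | about 0 |
| 5% vs 5% | 6.90% vs 6.90% | 0 | 1.20% | 39% |

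For 2% vs 1%: SE = √((0.0396 × 0.9604 + 0.0298 × 0.9702)/2424) = 0.526 pp, and Φ((1 − 0.98)/0.526 − 1.645) is about 5%. Because the difference is 0.98 times the excess in switching, an excess of 1/0.98 = 1.02 pp uses up the whole margin.

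**3. Switch censored.** Assume switches in 5% vs 1%, spread over the first 2 of 6 months, so that about 5 months remain on average. Baseline risk over that time is about 2% × 5/6 = 1.67%. If the hazard after a switch is h times higher, the intention-to-treat difference that censoring leaves out is about (5% − 1%) × (h − 1) × 1.67%.

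- h = 1: 0.
- h = 3: 0.04 × 2 × 1.67% = 0.13 pp.
- h = 5: 0.04 × 4 × 1.67% = 0.27 pp.

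**4. The initial phase (180 per arm).** Expected composite events are 180 × 0.02 = 3.6 per arm, and each switch counted as an event adds 1/180 = 0.56 pp to that arm.

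**The case against.** The best defence is that the switch sentence stands under missing values, goes on to exclude remaining time, and so most naturally means end of participation. It would then agree with the censoring in Modifications. That is plausible, and it removes the conflict between those two sections. It does not remove the conflict with Statistical analysis, because follow-up after the switch is still discarded.

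It can also be said that the estimand framework permits several strategies and that a SAP usually holds the detail. That is true of gaps, but here the protocol fixes rules that conflict, and no SAP could follow them all. Nor is analysis by allocation automatically the stricter choice: patients who cross to the comparator regimen can dilute a difference. This stands, and is why a supportive on-treatment analysis is needed.

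A reader might infer more than the text supports:

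- **That non-inferiority must fail whatever the true effect if switches count.** It need not. Equal 1% switching leaves about 66%. So does a true risk of 1% on ticagrelor vs 2% on control with switching of 2% vs 1%, since both arms then reach 2.98%.
- **That censoring biases the result by a known amount.** Nothing in the documents supports a three- to fivefold hazard. Modifications moves affected ticagrelor patients to standard care, for which Sample size assumes the same 2%. If risk is unchanged, the bias is nil.
- **That the anticoagulant clause is a rival switch rule.** It concerns a different event, and matters only because it too ends follow-up.
- **That "we will censor patients lost to follow-up and regard them as not having the primary endpoint" is a further contradiction.** That phrase is limited to Kaplan–Meier estimation and is a clumsy description of ordinary censoring. The stray word both in the intention-to-treat sentence is likewise only a slip.

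Finally, the figures at 2424 per arm describe the full trial. The initial phase has 180 per arm, where even without switches the chance of meeting the margin is Φ(1/1.476 − 1.645), about 17%.

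**Conclusion.** The concern holds. On the literal reading, switches enter the primary endpoint; on the benign reading, follow-up after a switch is dropped. Neither yields the intention-to-treat result on which non-inferiority is to be judged.

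The size depends on switch rates that the documents do not give. Counted as events, an excess of about 1 pp in the ticagrelor arm is enough to decide the full trial: 2% vs 1% gives 0.98 pp and cuts the chance of success from 80% to about 5%. Under censoring the illustrated effect is smaller, 0.13 to 0.27 pp for 5% vs 1% switching, and exists only if risk rises after a switch. These figures illustrate sensitivity to the rule and do not predict the trial's result. The sample size calculation itself is not in error.

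**What to change.** For the primary intention-to-treat analysis:

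- Remove the switch-as-endpoint sentence, with its exclusion of later time, from Treatment of missing values. Remove the censoring sentences from Modifications and Concomitant care.
- State one rule: all randomised patients are followed by allocation to the primary time point whatever they take, only adjudicated components of the composite count as events, and censoring occurs only at last known contact.
- Add one supportive on-treatment analysis that censors at the switch, judged against the same 1 pp margin. Agreement in direction is not a usable criterion: with a true difference of zero, the sign of each estimate is close to a coin flip.

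The clinical rules on switching stay unchanged; only their handling in the analysis is altered. The cost is protocol and SAP wording plus one extra analysis. The visits at 1, 3, 6 and 12 months and the monthly calls already planned can supply the follow-up after a switch.
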